## Introduction

In stroke, motor paresis being a major manifestation, has always been emphasized upon. However, subtle somatosensory impairments such as reduced ability of light touch, proprioception, stereognosis, and 2-point discrimination may also be exhibited among the poststroke subjects. Up to 2/3rd of the stroke subjects may experience impairment in any of the somatosensory modalities [1, 2].

The sensory deficits hamper the ability to utilize the available motor level in the functional tasks. The sensory recovery has been found to be strongly associated with the level of motor recovery. The impaired sensation along with the complex motor deficits increases the disability manifold. For instance, an individual with diminished light touch in hand despite good finger control may not be able to manipulate an object for functional performance. The sensory impairment is also associated with the participation restriction leading to poor quality of life [3]. Thus, integration of sensory abilities is crucial for the motor recovery.

In poststroke, sensory training of varied range has been investigated [4, 5]. The techniques may range from passive techniques such as somatosensory electrical stimulation to active retraining of stereognosis, proprioception, discriminating and localizing sensations However, most of them have not exhibited sufficient evidence for their effectiveness. Additionally, most of these techniques were not utilizing the theoretical foundation of neuroplasticity. Very few studies utilized the sensori-motor training, fulfilling some of the principles of neuroplasticity. Diego et al (2013) [6] investigated the effect of sensorimotor therapy in form of constraint induced movement therapy on chronic stroke. The construct of program had components of passive motor therapy, proprioception and touch inputs along with functional training. However, the chronic subjects of 4 to 5 years and only 16 h of therapeutic sessions were not favourable for the biological recovery [7]. Carey et al (2011) [8] conducted a randomized controlled trial by providing somatosensory discrimination training for texture and object recognition, and proprioception. The investigation exhibited favourable change for sensory recovery. However, the duration was only for 10 h with a low frequency of 3 h/week as well as the impact on the motor recovery was not examined.

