#### Sample size

The power calculation has been conducted using the values for motor and sensory assessment from the two different studies [9, 10]. Considering the beta = 0.1 and α = 0.05, the calculation inferred that 53 subjects in each group would be sufficient to detect the desired change. However, to compensate possible drop outs (15%), 61 subjects in each group will be enrolled. Thus, the total sample size for the proposed investigation will be 122.

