#### Allocation

The subjects will be randomly allocated between the experimental and control groups in a block of 10. The randomization process will be conducted by an office staff, not associated with the study, using the SPSS Version 23 software. The intervention will be allocated in the ratio of 1:1. The assignment will be serially arranged in the coded digital files. The principal investigator ([name]) will enroll the potential participants and assign them into the respective group. The assessor will be unaware about the group allocation of the subjects.

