### Eligibility criteria

The subjects will be recruited if they exhibit the following key criteria: 1) Age - 20 to 80 years, 2) Hemiparesis (right or left) (as assessed by Fugl-Meyer assessment [11] upper extremity subsection: 0 to 66), 3) First episode of unilateral stroke, 4) Ischemic or hemorrhagic stroke, 5) 1 to 12 months after the stroke onset, 6) Impaired or more sensory deficit of any of the sensory modalities (< 7/8) [1] as discerned by Nottingham Sensory Assessment (Erasmus MC modification of the revised version) [12], and 6) Able to comprehend instructions and perceive assessments. However, the participants will be excluded if they demonstrate any of the following: 1) Receptive communication or other language disorder (which could interfere with the assessment and treatment process), 2) Contractures and deformities of hand / finger, 3) Complex regional pain syndrome, 4) Severe cognitive or perceptual deficit (as evaluated by the National Institutes of Health Stroke Subscales [13] and clinical tests: copying and drawing, line-bisection, cancellation tasks, and functional performance), 5) Diabetic or any other neuropathy, 6) Skin disorder, and 7) Peripheral nerve injury of either of the upper limbs.

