#### Statistical methods

The data will be analyzed by using IBM SPSS version 23.0. The demographic and baseline features of the study participants will be analyzed in form of mean (SD) / median (IQR) / n (%) and appropriate test [(Mann-Whitney U (U) / independent t (t) / chi-square (χ^2^)] tests will be used to analyze the difference for the characteristics between the groups. For inferential statistics, an intention-to-treat analysis method will be used by carrying forward the last observation for the missing data. A repeated-measures 2-way ANOVA (continuous data; within factor, time; between factor, group) will be used to estimate difference for the post intervention and follow-up scores between the groups. The pre-intervention score will be considered as the covariate with group as the independent variable and post-intervention or follow-up score as the dependent variable. The significance level will be set at *P* < .05.

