### Perspective

The proposed study will lead to development, a novel rehabilitation protocol for the management of sensory-motor deficits in stroke. NEPSER trial represents the role of somatosensory training based on the concepts of neuroplasticity; in terms of key principles and application manoeuvre. The crucial components are frequency and intensity of protocol, recovery stage and chronicity of stroke, and management for specific sensory-deficit type. Most importantly, the integration of motor and sensory tasks has been systematically incorporated into the sensory protocol. It is hypothesized that the NEPSER regime will not only enhance the sensory recovery but also the motor and functional recovery. The improved sensation and motor activity may allow the subjects to utilize the paretic upper limb in daily performances. This may reduce the impact of stroke disability and enhance the quality of life.

The recruitment for the study has been started from October 2019 and expected to be completed by July 2022. The data from the proposed investigation will also provide the information about the various types of sensory deficits and their interaction with the motor recovery. In addition to this, the study findings will provide directions to consider sensory aspects in poststroke motor rehabilitation.

In view of various factors associated with the stroke, some of possible limitations of this study could be heterogeneity of the potential study subjects in terms of area of brain involvement, modality of sensory deficit, and motor recovery stages.

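### The between-group model adjusts only for the pre-intervention score; months since stroke should be pre-specified as a second covariate, for a modest gain in precision

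*Protocol article*

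**What the plan says.** All references are to the protocol article.

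- **Statistical methods.** The main model is given as follows: "A repeated-measures 2-way ANOVA (continuous data; within factor, time; between factor, group) will be used to estimate difference". On adjustment it adds: "The pre-intervention score will be considered as the covariate with group as the independent variable". The dependent variable is the score at post-intervention or at follow-up. No other covariate is named, and none is excluded. Baseline characteristics are to be compared between groups with significance tests, and no consequence of those tests is stated.
- **Eligibility criteria.** Entry is allowed "1 to 12 months after the stroke onset".
- **Allocation.** Patients are "randomly allocated between the experimental and control groups in a block of 10", with a 1:1 ratio. No stratification factor is mentioned.
- **Sample size.** With beta 0.1 and alpha 0.05, "53 subjects in each group would be sufficient to detect the desired change"; 61 per group are to be enrolled.
- **On chronicity.** The Introduction faults an earlier trial partly because its patients were 4 to 5 years after stroke, which it regards as unfavourable for biological recovery. Aim of the trial describes a programme tailored to stage and chronicity. Perspective says: "The crucial components are frequency and intensity of protocol, recovery stage and chronicity of stroke".

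**The concern.** The pre-score records how impaired a patient is at entry. It does not record when in the course of recovery that level was measured. Two patients with the same Fugl-Meyer score, one at month 1 and one at month 12, enter the model identically, although the article's own reasoning suggests that chronicity bears on how far they can recover. Time since stroke is handled neither in the allocation as described nor in the model as described.

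At stake is precision. Variance that an already known baseline variable could explain widens the confidence interval and costs some power. In addition, if the arms differ by chance in months since stroke, the single realised comparison is not adjusted for it. The planned baseline tests might show such a difference, but they do nothing about it.

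**Working it through.** **The plan's own figure.** The 53 per group cannot be reproduced, because Sample size gives no difference and no SD. It can only be solved backwards (normal approximation, 90% power, 1:1):

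- d = (z for alpha + z for power) × √(2/53)
- Two-sided 5% (assumed; sidedness is not stated): (1.960 + 1.282) × 0.1943 = 0.630
- One-sided 5%: (1.645 + 1.282) × 0.1943 = 0.568

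The 61 enrolled matches 53 × 1.15 = 60.95.

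**Gain from adding time since stroke.** Let R2 be the share of residual variance, after the pre-score, that time since stroke explains. The article gives no value, so I assume a range. The residual SD is multiplied by √(1 − R2), and

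power = Φ( d√(n/2) / √(1 − R2) − 1.960 ).

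With d = 0.630, d√(n/2) is 3.2415 at n = 53 and 3.478 at n = 61. For example, at n = 53 and R2 = 0.05: 3.2415/0.9747 − 1.960 = 1.366, and Φ = 91.4%.

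| R2 (assumed) | Power, 53 per arm | Power, 61 per arm | n per arm for 90% power, 53(1 − R2) rounded up |
|---|---|---|---|
| 0 | 90.0% | 93.5% | 53 |
| 0.02 | 90.6% | 94.0% | 52 |
| 0.05 | 91.4% | 94.6% | 51 |
| 0.10 | 92.7% | 95.6% | 48 |
| 0.20 | 95.2% | 97.3% | 43 |

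The 61-per-arm column applies if everyone enrolled is analysed, since the plan carries the last observation forward. It treats carried-forward values as equally informative, so it is an upper figure. With a one-sided test the gain is similar: at 53 per arm, 2.926/0.9747 − 1.645 = 1.358 gives 91.3% at R2 = 0.05, and 2.926/0.8944 − 1.645 = 1.627 gives 94.8% at R2 = 0.20.

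**Chance imbalance.** Assume entry times are uniform over 1 to 12 months:

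- SD = 11/√12 = 3.18 months
- SE of the difference in arm means at 53 per arm = 3.18 × √(2/53) = 0.62 months
- 95% range = ±1.21 months, or ±0.38 SD

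At the edge of that range the unadjusted estimate moves by 0.38 × √R2, which is 0.09, 0.12 and 0.17 residual SD for R2 = 0.05, 0.10 and 0.20. The back-solved effect is 0.63 SD.

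**Is the planned analysis invalid?** I simulated 20,000 trials per scenario at 53 per arm, with uniform entry times unrelated to the pre-score, and compared pre-score only with pre-score plus time since stroke.

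| R2 | Type I error, pre-score only | Mean estimate, pre-score only (true 0.630) | Power, pre-score only | Power, with time since stroke |
|---|---|---|---|---|
| 0.05 | 5.0% | 0.632 | 89.5% | 90.6% |
| 0.10 | 5.2% | 0.630 | 89.0% | 92.0% |
| 0.20 | 4.9% | 0.631 | 89.3% | 94.7% |

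The model with the pre-score alone holds its error rate and is unbiased. The difference between the models is in power only.

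**The case against.** The strongest objection is that nothing here is an error. Adjusting for the baseline value of the outcome is standard and valid. The article does not call the pre-score the sole covariate, and further covariates may stand in a full protocol or analysis plan that is not shown. This stands as far as validity goes. It does not remove the point, because the article is not silent: it states a specific covariate and leaves out a variable that every patient must have on record to be eligible.

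Four stronger readings are tempting and are not supported:

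- **That omitting time since stroke biases the result.** Randomisation keeps the estimate unbiased over repeated trials. The shifts of 0.09 to 0.17 SD are ordinary sampling variation, already reflected in the confidence interval and the 5% error rate.
- **That a known amount of recovery-related variance is being ignored.** Support in the article is qualitative only. The Perspective and Aim of the trial statements describe the intervention, and no figure shows how well months since onset predict either primary scale once its baseline is in the model. An R2 of 0.02 fits the article as well as 0.20 does.
- **That the baseline score of the other primary domain must also be added.** The Introduction says: "The sensory recovery has been found to be strongly associated with the level of motor recovery". That does not show that a baseline sensory score predicts later motor score given baseline motor score, or the reverse. A log scale for months has no basis in the article either.
- **That the baseline tests are meant to correct imbalance or select covariates.** The article gives them no such role.

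**Conclusion.** The point holds as a modest, low-cost improvement in efficiency; the planned analysis is valid without it. As described, neither the model nor the randomisation uses time since stroke, although entry spans 1 to 12 months and the article treats chronicity as relevant to recovery.

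Over an assumed R2 of 0.02 to 0.20, the gain is about 1 to 5 percentage points of power at 53 per arm. If all 61 per arm are analysed, it is about 1 to 4 points for R2 of 0.05 to 0.20. These sizes rest on the assumed R2, on an effect of 0.63 SD back-solved from the sample size, and on a two-sided 5% test. Only the covariate for time since stroke is firmly supported by the article.

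**What to change.** Add one sentence to Statistical methods, before the data are analysed: in the primary between-group model for each primary scale, months since stroke onset (continuous) is included as a covariate alongside the pre-intervention score, and is kept whatever the baseline significance tests show. The baseline score of the other primary domain may be added as an option; if so, it should be fixed in the same sentence.

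The cost is one degree of freedom (102 instead of 103 residual at 53 per arm). No new data are needed, because time since onset is established at eligibility. Stratifying the randomisation would be the alternative, but recruitment began in October 2019, so it could not cover patients already allocated. The covariate covers everyone.

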### Perspective

The proposed study will lead to development, a novel rehabilitation protocol for the management of sensory-motor deficits in stroke. NEPSER trial represents the role of somatosensory training based on the concepts of neuroplasticity; in terms of key principles and application manoeuvre. The crucial components are frequency and intensity of protocol, recovery stage and chronicity of stroke, and management for specific sensory-deficit type. Most importantly, the integration of motor and sensory tasks has been systematically incorporated into the sensory protocol. It is hypothesized that the NEPSER regime will not only enhance the sensory recovery but also the motor and functional recovery. The improved sensation and motor activity may allow the subjects to utilize the paretic upper limb in daily performances. This may reduce the impact of stroke disability and enhance the quality of life.

The recruitment for the study has been started from October 2019 and expected to be completed by July 2022. The data from the proposed investigation will also provide the information about the various types of sensory deficits and their interaction with the motor recovery. In addition to this, the study findings will provide directions to consider sensory aspects in poststroke motor rehabilitation.

In view of various factors associated with the stroke, some of possible limitations of this study could be heterogeneity of the potential study subjects in terms of area of brain involvement, modality of sensory deficit, and motor recovery stages.

## Data Availability

Not applicable.

## Abbreviations

BRS-H: Brunnstrom Recovery Stage – Hand
Em-NSA: Erasmus MC modification of the revised Nottingham Sensory Assessment
FMA: Fugl-Meyer Assessment
mRS: Modified Rankin scale
MT: Mirror therapy
NEPSER: **NE**uroplasticity-**P**rinciples-based **SE**nsory-**R**ehabilitation
NSA: Nottingham Sensory Assessment
SPIRIT: Standard Protocol Items: Recommendations for Interventional Trials
SWM: Semmes-Weinstein monofilaments
UE: Upper extremity
2PD: Two-point discrimination test
